#### Booster session (evaluation)

In this session the past months will be discussed and goals will be evaluated. New goals will be set. In addition, the trainers will motivate the participants to bring up a topic for the booster.

### Nurse training

The BGI course will be given by trained practice nurses (n = 3). They receive two 3-h training sessions from the psychologist who is familiar with the BGI training (Train-the-trainer principle). During the training they will work with the five-step proactive coping plan and will be taught on the principles of the self-regulation and pro-active coping theory. The practice nurse should have the role of facilitator and coach, stimulating participants to support each other and become self-confident in seeking information.

### Control group

As stated above, participants in the control group will receive similar diabetes care as those in the intervention group, according to the guidelines of the Dutch College of General Practitioners [16]. The only difference between both groups will be the additional BGI course.

### Outcome measures

#### Primary outcome measure

The primary outcome measure will be the same as in the original BGI study for comparison reasons and is therefore; change in BMI (difference of 0.77 kg/m^2^ is considered clinical relevant) between baseline and follow-up (2.5 years after the start of the BGI program).

#### Secondary outcome measures

The secondary outcomes will be change between baseline and 2.5 years follow-up of:Clinical measures: systolic blood pressure, HbA1c, lipid profile (total cholesterol, LDL, HDL, triglycerides);Diabetes self-management behaviour (self-care, physical activity, dietary intake, medication adherence);Proactive coping;Quality of Life;Cost-effectiveness of the intervention (total health care resources use during the entire study period).

### Measurements

#### Clinical measures

In both groups, BMI, systolic blood pressure, HbA1c and lipid profiles will collected from the electronic medical record at baseline and 2.5 years follow-up. Clinical measures in-between will also be extracted from the electronic medical record of the GP.

#### Questionnaires

Participants will be asked to complete questionnaires to measure diabetes self-management behaviour, proactive coping and quality of life at baseline and 2.5 years follow-up, with the following measures.

#### Diabetes self-management behaviour

The SDSCA, revised according to Toobert et al. [19], includes eleven items assessing several aspects of the diabetes regimen: general diet, specific diet, exercise, blood glucose testing, foot care, and smoking. Ten items are rated on an 8-point Likert scale, measuring how many days an activity is performed in the last week. One item measures smoking status (yes/no) and the amount of cigarettes smoked in the last week. Each of the domains is measured separately.The PASE questionnaire [20] includes 15 items, which cover leisure time physical activities (six items), household physical activities (six items), and work related physical activities (three items). Items differ in scoring range and are translated to the time spent on each activity into a composite score which reflects the amount of energy expended.The ‘Kristal food habits questionnaire’ [21] consists of 22 items assessing patient’s habits with regard to fatty food intake, dietary products and fruit and vegetable intake. The items differ in scoring ranges.The MARS-5 [22], is a brief 5-item instrument which assesses the degree to which patients forget medication, stop taking their medication or change dosages. Items range from 1 (always–never adherent) to 5 (never–always adherent).

#### Proactive coping

Proactive coping will be measured with the ‘Proactive Diabetes Management Inventory’ (PDMI) [17], designed to evaluate the success of our course in getting patients to implement the five-step plan in their self-care. The instrument includes 7 statements covering different aspects of the five-step plan. The first six items assess whether patients think about their goals beforehand in a proactive fashion; that is, do they anticipate the conditions needed to reach their goal and do they anticipate barriers they may encounter along the way? Items 7–12 assess whether patients anticipate and plan the strategies needed to achieve their goal. Finally, Items 13–17 assess whether patients monitor their progress and strategies and adapt these accordingly. The items range from 1 (definitely not) to 5 (definitely) [17].

#### Quality of life

The EuroQol EQ-5D, Short-Form 36 (SF36) and a diabetes-specific quality of life questionnaire, namely the Audit of Diabetes-Dependent Quality of Life (ADDQol) will be used to measure health-related quality of life as well as health status.The EQ 5D is a generic quality of life questionnaire, consisting of a Visual Analogue Scale (EQ 5D-VAS) and a classification system (EQ 5D-Profile) [23]. The EQ 5D-Profile covers five domains: mobility, self-care, usual activities, pain/discomfort and anxiety/depression of health, each with three levels of functioning: level 1, no problems; level 2, some problems; level 3, severe problems. The EQ-5D health utility scores range from −0.33 to +1.00 and were computed using the Dutch tariff as described by Lamers et al. [24, 25]. A score of 0 is equal to death, whereas 1 indicates full health. Negative values represent a health state worse than death. The EQ 5D-VAS is a graduated, vertical line, anchored at 0 (worst imaginable health state) and 100 (best imaginable health state). The patient is asked to mark a point on the EQ 5D-VAS that best reflects his/her actual health state.The SF-36 generates a profile of scores on eight dimensions of health status: Physical Functioning (10 items), Role Physical (4 items), Bodily Pain (2 items), General Health (5 items), Vitality (4 items), Social Functioning (2 items), Role-Emotional (3 items) and Mental Health (5 items). These scales can be summarised in Physical Health and Mental Health. The 36 items differ in the scoring ranges [26].The ADDQoL, measures the perceived impact of diabetes on the quality of life; it includes 19 items, ranging from −3 to 3 on different questions, with 0 as the neutral score. Scores below 0 reflect a negative influence of the item on quality of life, and those above 0 reflect positive influences. The impact scores are weighted (impact rating x importance rating), so the actual scores per item can range from −9 to 9 [27].

#### Cost-effectiveness

Data on health care resources use during the whole study period will be extracted from electronic medical records from the general practitioners and for health status the EQ 5D questionnaire will be used at baseline and after 2.5 years follow-up.

### Sample size

In our previous study, the self-management intervention BGI achieved a significant BMI reduction of 0.77 after 9 months in screen-detected T2DM patients (BMI −0.39 in the intervention group vs. +0.38 in the control group) [2]. For the current study a minimum sample size of 88 (44 per group) is required to achieve 80% power to detect a difference of 0.77 in a design with 6 repeated measurements of BMI (weight is measured every three months as part of usual diabetes care) having a AR (1) covariance structure when the standard deviation is 1.7, the correlation between subsequent observations on the same subject is 0.70, and alpha 0.05. With an expected drop-out rate of 20%, we need to include a total of 106 patients.

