**Methods:**

Randomised controlled trial with 2.5 year follow-up. Adults (≤75 years) with a type 2 diabetes duration between 3 months and 5 years will be included. With the use of a self-management screening tool (SeMaS) their potential barriers of self-management due to depression and/or anxiety will be determined. Based on the results of the SeMaS selection patients will be randomised (1:1) to the BGI-group (n = 53) or the control-group (n = 53). In addition to receiving usual care, patients in the BGI-group will follow the 12-week theory-based self-management program and a booster session a few months thereafter. The control-group will receive care as usual. The primary outcome is change in Body Mass Index after 2.5 years follow-up. Secondary outcomes are HbA1c, lipid profile and systolic blood pressure, (diabetes) quality of life, level of physical activity, dietary intake and medication adherence and proactive coping. Cost-effectiveness will be based on total use of health care resources during the entire study period. Difference between groups in change over time will be analysed according to intention-to-treat analysis.

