### Statistical analyses

The efficacy analysis will be performed by intention-to-treat analysis, including all patients from whom a follow-up assessment is available. If necessary a multiple imputation technique will be used for missing data. The primary outcome will be analysed by using Generalized Estimated Equations (GEE) for repeated measures, with baseline BMI as covariate and time, intervention and the interaction of time and intervention as fixed variables. The secondary outcomes will be analysed with ANCOVA on the change from baseline to follow-up. In addition differences in characteristics (e.g. age, sex, education level) of participants and non-participants will be evaluated.

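### The 80% power fits a BMI difference averaged over six measurements; for the primary outcome, the change at 2.5 years, the plan's own inputs give about 57%

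*Protocol article*

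**What the plan says.** Three sections of the protocol article bear on this point.

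- **Outcome.** The abstract states: "The primary outcome is change in Body Mass Index after 2.5 years follow-up". The section Primary outcome measure likewise defines the change "between baseline and follow-up (2.5 years after the start of the BGI program", and calls 0.77 kg/m2 clinically relevant.
- **Sample size.** The trial is sized "to detect a difference of 0.77 in a design with 6 repeated measurements of BMI (weight is measured every three months", "having a AR (1) covariance structure", "when the standard deviation is 1.7", and where "the correlation between subsequent observations on the same subject is 0.70". Alpha is 0.05. The result is 44 per group for 80% power, raised to 106 in total (53 per group) for dropout. The 0.77 is the difference that the previous study saw at 9 months.
- **Analysis.** The section Statistical analyses specifies GEE for the primary outcome, "with baseline BMI as covariate and time, intervention and the interaction of time and intervention as fixed variables". It does not name the contrast that is the primary test.

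**The concern.** A sample size formula for repeated measurements gains precision by averaging each patient's noise over several visits. That gain belongs to a hypothesis about the average difference over those visits. It does not carry over to a difference at the last visit, which is what the outcome section asks about.

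The averaged calculation also assumes that the full 0.77 is present at every measurement. Whether a 9-month effect lasts to 2.5 years is the question this trial was set up to answer. The Background itself cites a trial of another education programme in which a weight benefit at one year was no longer apparent at three years.

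If the 80% is attached to the wrong quantity, a null result at 2.5 years would be read as coming from an adequately powered trial when the chance of detecting 0.77 was not far above one half.

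**Working it through.** **Inputs** (all from Sample size unless noted): difference 0.77; SD 1.7; AR(1) with correlation 0.70 between subsequent observations; 6 measurements; alpha 0.05, taken as two-sided; power 80%; 44 per group required and 53 enrolled. Time point of the outcome: 2.5 years (Primary outcome measure). Normal approximation throughout.

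**1. Reproduce the plan's figure.** Variance factor for a patient's mean over six AR(1) measurements:

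(1/36) × [6 + 2 × (5×0.7 + 4×0.49 + 3×0.343 + 2×0.2401 + 1×0.16807)] = 20.2745/36 = 0.5632

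n per group = 2 × (1.960 + 0.842)² × 1.7² × 0.5632 / 0.77² = 43.1, so 44. Power with 44 is 80.8%. The plan's figure reproduces.

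Other readings of the same inputs do not give 44 per group:
- one-sided test of the mean: 34
- GLS-weighted mean: 41
- five visits: 48; seven visits: 40
- compound symmetry over six visits: 58
- baseline-adjusted mean over five or six later visits: 36 or 35
- single visit: 77
- single visit adjusted for a baseline correlated at 0.70: 40

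**2. Same inputs, one time point.** Standard error = √(2 × 1.7²/44) = 0.362. Power = Φ(0.77/0.362 − 1.960) = Φ(0.165) = 56.5% (55.6% with the t distribution). The answer is the same 56.5% if 1.7 is the SD of the change.

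**3. With baseline BMI as covariate.** The SD becomes 1.7 × √(1 − r²), where r is the correlation between baseline and 2.5 years. Extending AR(1) 0.70 to baseline:
- lag 5 (r = 0.7⁵ = 0.168): SD 1.676, power 57.7%
- lag 6 (r = 0.7⁶ = 0.118): power 57.1%
- lag 10, if 0.70 applies quarterly over 2.5 years (r = 0.028): power 56.6%

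**4. All 53 per group evaluable.** Unadjusted: 64.5%. Adjusted at lag 5: Φ(0.77/(1.676 × √(2/53)) − 1.960) = Φ(0.405) = 65.7%.

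**5. Difference detectable with 80% power, 44 per group.** 2.802 × 1.7 × √(2/44) = 1.02 kg/m2. Conversely, 80% power for 0.77 at one time point needs 2 × 7.849 × 2.89/0.5929 = 76.5, so 77 evaluable per group (75 with lag-5 adjustment).

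**6. What would restore 80%.** The adjusted SD would have to be 0.77/(2.802 × √(2/44)) = 1.289. So 1 − r² = (1.289/1.7)² = 0.575 and r = 0.65. If 1.7 is a raw SD, power with 44 per group is 69% at r = 0.5, 76% at 0.6 and 84% at 0.7.

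**The case against.** The strongest objection concerns the correlation. The article does not say whether 1.7 is the SD of BMI at a visit, of the change, or a residual SD. Nor does it say whether baseline is one of the six measurements. If 1.7 is a raw SD and all six measurements follow baseline, the article gives no baseline to 2.5-year correlation, and step 3 extends AR(1) to a point the text does not explicitly cover. A correlation of 0.70 would give 84% power. This stands as a condition on the 57%: one cannot say that the stated structure excludes higher power. But 0.70 is given only for subsequent observations, and under AR(1) it decays with distance, so nothing in the article points to 0.65 or more across 2.5 years. Nor is 57% the least favourable reading: if 1.7 is the per-visit SD and an unadjusted change score is used, power is 33–38%.

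Two stronger readings are tempting, and the article does not support them.

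- A reader might infer that the GEE model tests yet another hypothesis, a difference in slopes, so that three primary tests compete. The section Statistical analyses does not say that time is linear or that the interaction coefficient is the test. With categorical time, the same model yields the 2.5-year contrast directly, so it is compatible with the outcome definition. What is missing is only the name of the contrast.
- A reader might infer that the six measurements stop at 15–18 months. The remark about three-monthly weighing describes usual care. It does not say that the six analysed values are consecutive quarterly ones, and baseline plus five half-yearly values spans exactly 2.5 years. The spacing is ambiguous, not shown to be wrong.

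It may also be said that the repeated-measures model recovers power at the last visit. With categorical time it adds essentially nothing beyond the baseline adjustment. Even if time were modelled as linear, the fitted difference at the last visit would have 58–59% power with five or six post-baseline visits and 63–64% with ten.

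**Conclusion.** The concern holds for the mismatch between the power statement and the primary outcome. The sample size arithmetic is correct for the quantity it evidently describes, but that quantity is not the primary outcome. With 44 evaluable per group, power for 0.77 at 2.5 years is about 57%, a shortfall of some 23 percentage points from the stated 80%.

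This rests on three assumptions: two-sided alpha, which the reproduction supports; an SD of 1.7 that applies at 2.5 years, or is the SD of the change; and, for the adjusted figures, AR(1) extended to baseline. That the 80% refers to a visit average is inferred from exact reproduction, not from the article's wording.

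**What to change.** - **Statistical analyses:** name the baseline-adjusted BGI minus control contrast at the 2.5-year visit, from the GEE with time categorical, as the primary test.
- **Sample size:** restate the power for that contrast as about 57% for 0.77 with 44 evaluable per group, and 80% for a difference of about 1.0 kg/m2. Say what the SD of 1.7 refers to. If a higher baseline to 2.5-year correlation is to be relied on, state it and its source.
- **Measurement schedule:** state how many BMI values enter the model, at what spacing, and whether baseline is one of them, so that they visibly cover 2.5 years.
- **Visit average:** report the difference averaged over visits as a secondary analysis with its own power. That power depends on the schedule: with ten quarterly visits the variance factor is 0.4155 and 44 per group gives 91%, so the 80% could not simply be carried over.

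The cost is wording in two sections and a less favourable power statement. No extra patients or data are needed.

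### The sample size rests on six BMI measurements attributed to three-monthly weighing, a design that covers 15 to 18 months, while the primary outcome is the change at 2.5 years

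*Protocol article*

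**What the plan says.** Four places in the Methods of the protocol article bear on this.

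- **Sample size.** The calculation aims "to achieve 80% power to detect a difference of 0.77" and does so "in a design with 6 repeated measurements of BMI (weight is measured every three months as part of usual diabetes care"). The parenthesis is the only explanation of where these measurements come from. The other inputs are an AR(1) structure, SD 1.7, correlation 0.70 between successive observations and alpha 0.05. The result is 44 per group, 88 in total, raised to 106 for drop-out.
- **Primary outcome measure.** The outcome is the change in BMI "between baseline and follow-up (2.5 years after the start of the BGI program"), that is, at month 30.
- **Clinical measures.** "BMI, systolic blood pressure, HbA1c and lipid profiles will collected from the electronic medical record at baseline and 2.5 years follow-up". It adds: "Clinical measures in-between will also be extracted from the electronic medical record of the GP". Neither the number nor the timing of the intermediate values is given.
- **Statistical analyses.** The primary model is a GEE for repeated measures, "with baseline BMI as covariate and time, intervention and the interaction of time and intervention as fixed variables". No time points are listed, and it is not said which contrast from the model is the primary result.

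**The concern.** The Sample size section gives a count (six) and a source (weighing every three months). Together these describe a design of 15 to 18 months, and the primary outcome is at 30 months. The article does not explain the difference.

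The count matters because it produces the sample size. Under AR(1), the variance of an average over visits depends on how many visits there are and how strongly they correlate, so changing the grid changes the required number. The quoted 80% also belongs to a difference averaged over the visits, whereas the primary outcome is a change at one time point. As the text stands, a reader cannot tell what power the trial has for the question it was set up to answer, the effect at 2.5 years.

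**Working it through.** **Calendar.** Six quarterly values span (6 − 1) × 3 = 15 months if baseline is one of them, or 6 × 3 = 18 months if all follow baseline. The endpoint is at 30 months, so the span is 12 to 15 months short, or 40% to 50% of follow-up. Quarterly weighing to month 30 gives 30 / 3 = 10 follow-up values, or 11 with baseline.

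**Inputs from Sample size.** Difference 0.77, SD 1.7, adjacent correlation ρ = 0.70, m = 6, alpha 0.05 (taken as two-sided), power 80%.

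**Reproducing the plan's figure.** For a difference averaged over m AR(1) values:

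n per group = 2 × SD² × (1.96 + 0.84)² / 0.77² × VF, where VF = (1/m²) × Σᵢ Σⱼ ρ^|i−j|

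- The part before VF is the requirement for a single value: 76.5, rounded up to 77.
- For m = 6, VF = [6 + 2 × (5 × 0.7 + 4 × 0.49 + 3 × 0.343 + 2 × 0.2401 + 0.16807)] / 36 = 20.27 / 36 = 0.563.
- n = 76.5 × 0.563 = 43.1, rounded up to 44. This is the stated figure. Power at 44 is 80.8% by the normal approximation and 79.9% by the noncentral t.

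Other readings miss 44. One-sided alpha gives 34 and five values give 48. The stated number therefore depends on the count of six.

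**The same inputs on other grids.**

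| Quantity and grid | VF | n per group | Power at 44 per group |
|---|---|---|---|
| Average, 6 values, adjacent ρ 0.70 | 0.563 | 44 | 80.8% |
| Average, 10 quarterly follow-ups, ρ 0.70 | 0.416 | 32 | 90.9% |
| Average, 11 quarterly values with baseline, ρ 0.70 | 0.389 | 30 | 92.6% |
| Average, 6 six-monthly values, ρ 0.70 over three months (0.49 over six) | 0.384 | 30 | 92.9% |
| Month-30 value alone, SD 1.7 | 1 | 77 | 56.5% |

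If all 53 randomised per group supplied a month-30 value, the last row would rise to 64.5%.

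**How far the month-30 figure depends on assumptions.** The article does not say whether 1.7 is the SD of BMI, of its change, or of the baseline-adjusted value. Suppose it is the SD of BMI and baseline is a covariate. The working SD is then 1.7 × √(1 − r²), where r is the correlation between baseline and month 30.

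- AR(1) with 0.70 over three months: r = 0.70¹⁰ = 0.028; 77 per group; 56.6% power at 44.
- AR(1) with 0.70 over six months: r = 0.70⁵ = 0.168; 75 per group; 57.7% power at 44.
- r = 0.70 between baseline and month 30 directly, which departs from the stated AR(1) structure: 40 per group; 84.5% power at 44.

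Under the stated covariance structure the month-30 power stays near 57%. It exceeds 80% only if BMI tracks over 30 months far more closely than that structure implies.

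**The case against.** The strongest reply is that the parenthesis only describes how often usual care weighs patients and does not say that the six values are consecutive. Months 0, 6, 12, 18, 24 and 30 are six values, all fall on a quarterly routine, and they end at 2.5 years. If 0.70 is the correlation between adjacent values of that grid, the result is again 43.1, rounded up to 44. So it would be wrong to say that no grid reaching month 30 yields the stated number.

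This reading counts baseline as one of the repeated outcomes, whereas Statistical analyses makes baseline BMI a covariate. Without baseline, five follow-up values remain, and these need 48 per group (0.70 over six months) or 34 (0.70 over three months, so 0.49 over six). Six equally spaced values after baseline would need five-month spacing, and only months 15 and 30 of that grid coincide with quarterly weighing. The reading is possible, but the article states neither of the two things it needs.

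Three stronger inferences are tempting, and the article does not support them:

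- **That the primary analysis stops at month 15 to 18.** Clinical measures collects BMI at 2.5 years, and the GEE is not restricted to six values.
- **That the result is biased in favour of the programme.** The Background cites a trial whose one-year benefit had gone by three years, so an early cut-off could flatter the programme. But the analysts would have to set aside the month-30 BMI that they plan to collect and have made the endpoint. Nothing suggests that they would.
- **That the visit mismatch alone makes the trial too small.** For an averaged difference, more visits reduce the requirement, from 44 to 32 per group.

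It is also fair to say that visit windows and rules for choosing among recorded weights belong in an analysis plan. Their absence from an article is no fault.

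**Conclusion.** The point holds as an inconsistency in the stated design and power. The visit count, the only source given for it, and the 30-month horizon do not fit together as written, and the quoted 80% applies to an average over six values, not to the change at 2.5 years.

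The size depends on what is estimated. For an average over the ten quarterly follow-up values, the plan is better powered than stated, at about 91% with 44 per group. For the month-30 contrast alone it is at about 57%, provided 1.7 is the SD of the analysed month-30 value. That proviso is an assumption, and a strong direct correlation between baseline and month 30 would raise the figure to about 84%. All these figures take 0.77 as the true difference, two-sided alpha, and for the averaged figures the stated AR(1) structure.

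**What to change.** Reconcile Primary outcome measure, Clinical measures, Sample size and Statistical analyses:

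1. State the months of the BMI measurements that enter the GEE, through month 30, and whether baseline is one of them or only a covariate.
2. State the interval to which the correlation of 0.70 applies, and whether 1.7 is the SD of BMI, of its change, or of the baseline-adjusted value.
3. Name the between-group contrast at month 30, taken from the time-by-intervention model, as the primary estimate.
4. Restate the power for that contrast and grid at the planned sample size.

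This is a change of wording plus one recalculation. The intermediate weights are already to be extracted, so no visits are added, and no further patients need to be enrolled. The cost is that the restated power may be less favourable than 80%.

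### The 20% drop-out allowance was applied as 88 × 1.2 rather than 88 / 0.8, so the target of 106 does not leave the 88 patients the plan requires

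*Protocol article*

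**What the plan says.** The Sample size section of the protocol article gives the requirement first: "For the current study a minimum sample size of 88 (44 per group) is required to achieve 80% power". The target difference in BMI is 0.77 kg/m², and the calculation rests on "a design with 6 repeated measurements of BMI", "having a AR (1) covariance structure", and applies "when the standard deviation is 1.7, the correlation between subsequent observations on the same subject is 0.70, and alpha 0.05". The section ends with the recruitment target: "With an expected drop-out rate of 20%, we need to include a total of 106 patients". The Methods paragraph of the abstract carries that target forward as 53 patients in each arm. The article gives no other drop-out rate and no other base sample size.

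**The concern.** A drop-out rate is a proportion of the patients who enter the trial. To have 88 left after losing 20% of entrants, the base must be divided by 0.80. The plan's 106 looks like 88 increased by 20%, which protects against a smaller loss than the one assumed. If so, the recruitment target misses the plan's own minimum at the plan's own drop-out rate, and the claim of 80% power does not follow from the numbers beside it. The 20% allowance has no purpose other than to protect the 88.

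**Working it through.** **Inputs** (all from the Sample size section unless noted): difference 0.77; SD 1.7, so variance 2.89; 6 measurements; AR(1) correlation 0.70; alpha 0.05; power 80%; minimum 88, or 44 per group; drop-out 20%; target 106. The 53 per arm is from the abstract. Whether alpha is one- or two-sided is not stated, and no formula is named.

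**1. Reproduce the base of 88.** Assume two-sided alpha and a comparison of the simple mean of the six measurements.

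- Variance factor of the mean under AR(1): f = [6 + 2(5×0.70 + 4×0.70² + 3×0.70³ + 2×0.70⁴ + 0.70⁵)] / 36 = (6 + 14.275) / 36 = 0.5632.
- Per-group size: n = 2(1.960 + 0.842)² × 2.89 × 0.5632 / 0.77² = 43.09, rounded up to 44, so 88 in total.

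This matches the plan exactly. A one-sided alpha gives 34 per group, and an optimally weighted (generalised least squares) mean gives 41. Neither matches, so the two-sided simple-mean reading is used below.

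**2. Reproduce the 106.**

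| Inflation | Calculation | Result |
|---|---|---|
| Multiply by (1 + rate) | 88 × 1.2 = 105.6 | 106 (53 per group), as stated |
| Divide by (1 − rate) | 88 / 0.80 | 110 (55 per group) |

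Only the first gives the plan's figure.

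**3. What 106 leaves.**

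- At 20% drop-out: 106 × 0.80 = 84.8 patients, or 42.4 per group. The shortfall is 88 − 84.8 = 3.2, or 4 if 42 per group remain.
- Largest drop-out that still leaves 88: 1 − 88/106 = 17.0%.
- Check on 110: 110 × 0.80 = 88.

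**4. Power at the reduced size.** Power = Φ(0.77 / √(2 × 2.89 × 0.5632 / n) − 1.96).

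| n per group | Power |
|---|---|
| 44 | 80.8% |
| 43 | 79.9% |
| 42.4 | 79.4% |
| 42 | 79.0% |

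These figures count only the patients who remain and give drop-outs no weight.

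**The case against.** The arithmetic is hard to dispute, so the case on the other side concerns the consequence.

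First, the 88 contains rounding slack. The unrounded need is 43.09 per group, or 86.2 in total, so the shortfall against that is about 1.4 patients (86.2 − 84.8). At 42.4 per group the power is 79.4%, only 0.6 points under target. This is correct, but 42.4 is still below even the unrounded requirement.

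Second, drop-outs need not contribute nothing. The Statistical analyses section includes every patient with a follow-up assessment, uses GEE for repeated measures and allows multiple imputation. The Clinical measures section also takes intermediate values from the general practice record. As an illustration, suppose the 10.6 drop-outs per arm (20% of 53) leave evenly after 0 to 5 of the six measurements and are weighted by their information under the plan's AR(1) correlation. The trial then has the equivalent of about 48.7 complete patients per arm and roughly 85% power for the time-averaged comparison. If every drop-out supplies a single measurement, power is about 84%. The dropout pattern is an assumption and is not in the article. The point stands as a limit on the power claim: 79% is the case in which drop-outs add no data. It does not rescue the stated target, because the Sample size section takes no such credit and treats 88 as the number that must remain.

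Third, two patients per arm is less than the uncertainty in the SD, the correlation and the drop-out rate themselves. That is fair, and it is why the finding calls for a correction to a stated figure and does not question the design.

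**Conclusion.** The error is real and is settled by the plan's own figures: 106 does not follow from 88 and 20%. The target is four patients too low (110 − 106), and at the assumed drop-out it leaves 84.8 patients where the plan requires 88. The head count needs no assumption beyond reading the drop-out rate as a share of those included.

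The effect on power is minor: about 79% (79.0% to 79.4%) against the claimed 80%. That figure rests on two-sided alpha, the simple mean of six AR(1) measurements, and no data from drop-outs. With partial data, actual power may be above 80%. The analysis method and the risk of bias are unaffected.

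**What to change.** Correct the last sentence of the Sample size section in one of two ways.

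- **Keep 106 and state what it delivers.** For example: the target of 106 patients (53 per group) leaves 88 evaluable patients if drop-out does not exceed 17%; at 20% drop-out about 85 remain, with approximately 79% power if drop-outs contribute no data. This costs one sentence and leaves the abstract unchanged.
- **Restate the target as 110 (55 per group),** from 88 / 0.80. This costs four more patients, and the abstract must then read 55 per arm.

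The first option is enough to make the document consistent. Given the size of the discrepancy, there is no strong reason to insist on the second.
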